#### Sample size calculation

2.7.1

In this study, the sample size was estimated according to the difference in the change in 1-h pad test weight from baseline to week 6. The calculation was informed by both previously reported evidence on EA for SUI (7, 9) and findings from our unpublished pilot study (*n* = 40) in post-RP SUI patients, which utilized identical interventions and involved a patient population with comparable baseline characteristics. The pilot data demonstrated a mean reduction of 58.1 g (from 83.1 g to 25.0 g) in the EA plus PFME group, compared to a mean reduction of 29.7 g (from 85.5 g to 55.8 g) in the placebo EA plus PFME group. Collectively, these sources supported an assumed mean between-group difference (effect size) of 28.4 g for the primary outcome, with a pooled standard deviation (SD) of 48.87 g.

Using PASS 2021 software (Version 21.0.3; NCSS, LLC), with a two-tailed significance level set at *α* = 0.05% and 80% statistical power to detect the aforementioned effect size (mean difference = 28.4 g, SD = 48.87 g), the minimum required sample size was calculated to be 96 participants (48 per group). To account for an anticipated dropout rate of 20%, the total number of patients to be recruited for the study was set at 120.

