#### Statistical analysis of treatment efficiency

2.7.2

All statistical analyses will be conducted using SPSS software (version 29.0, IBM Corp.) by a statistician blinded to group allocation and intervention details. The analyses will follow the intention-to-treat (ITT) principle, with per-protocol analysis conducted as a supplementary assessment. Missing data will be handled under the missing-at-random assumption using sequential regression multiple imputation.

Baseline demographic and clinical characteristics will be summarized using descriptive statistics. Continuous variables will be summarized as mean (standard deviation) for normally distributed data or median (interquartile range) for non-normally distributed data, and compared using independent samples *t*-tests or Mann–Whitney *U* tests, respectively. Categorical variables will be presented as frequency (percentage) and analyzed using chi-square or Fisher's exact tests, as appropriate.

The primary analysis will adjust for some covariates, such as the time interval from surgery to enrollment, to account for the potential influence. Repeatedly measured outcomes (1-h pad test weight, ICIQ-UI-SF scores, and 24-h pad usage) will be analyzed using mixed-effects models for repeated measures. Treatment response rates will be compared between groups using binary logistic regression or chi-square test. Additionally, changes in pelvic structural parameters measured by MRI will be analyzed using an appropriate mixed-effects model. The incidence of adverse events will be compared between groups using chi-square or Fisher's exact test.

To explore potential heterogeneity of treatment effects, pre-specified subgroup analyses will be conducted based on the following baseline factors: baseline severity of incontinence (stratified by 1-h pad test weight), patient age, and time interval from surgery to enrollment.

All statistical tests will be two-sided, with a *P*-value <0.05 considered statistically significant, except where adjusted for multiple comparisons.

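### Heterogeneity of the treatment effect is explored through subgroups of continuously measured factors; a treatment-by-continuous-factor interaction would usually use the data better

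*Protocol article*

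**What the plan says.** Section 2.7.2 of the protocol article (Statistical analysis of treatment efficiency) states: "To explore potential heterogeneity of treatment effects, pre-specified subgroup analyses will be conducted". The factors are "baseline severity of incontinence (stratified by 1-h pad test weight), patient age, and time interval from surgery to enrollment". Only severity is expressly said to be stratified. Age and the interval since surgery are named without a form, although a subgroup analysis normally means that they are grouped. The article gives no number of groups and no cut points, and it mentions neither an interaction test nor separate tests within groups.

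All three factors are available as continuous measurements: pad weight in grams (section 2.6.3), age within an entry range of 45 to 80 years (section 2.3), and the time from surgery to enrollment (section 2.6.2). Section 2.7.2 already plans mixed models for the repeated outcomes and already adjusts the primary analysis for the interval since surgery.

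The trial is sized for the main effect only. Section 2.7.1 uses an "assumed mean between-group difference (effect size) of 28.4 g for the primary outcome" with an SD of 48.87 g, and "the minimum required sample size was calculated to be 96 participants (48 per group").

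**The concern.** The stated aim is to learn whether electroacupuncture works differently according to severity, age or time since surgery. Grouping a continuous factor treats all men in a group as alike and makes the answer depend on where the cut falls. Better-chosen cut points would not recover the variation within groups. This is therefore a question about the method named in the article, not about details that a statistical analysis plan would supply.

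What is at stake is the efficiency of an exploratory analysis in a trial that has little power for interactions in any case. The primary comparison does not depend on it.

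**Working it through.** **1. The plan's own figure.** Inputs from section 2.7.1: difference 28.4 g, SD 48.87 g, power 80%, two-sided test. Section 2.7.1 prints the significance level as 0.05%, while section 2.7.2 uses P < 0.05. I use 5%, because only that reproduces the stated size.

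- Normal approximation: n per group = 2 × (1.960 + 0.842)² × 48.87² / 28.4² = 46.5, so 47.
- Noncentral t: power is 0.796 with 47 per group and 0.804 with 48, so 48 per group and 96 in total, as stated. Allowing for 20% dropout, 96 / 0.80 = 120, as stated.
- With 0.05% taken literally, the normal approximation needs 111 per group.

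**2. Information kept after grouping.** If the treatment effect changes linearly with a factor, the share of information kept is the squared correlation between the factor and its grouped version, each group being scored by its mean. For a median split of a normal factor this is 2/π = 0.637, a loss of 36%, so that 96 men act like 96 × 0.637 = 61. The article gives neither the distributions nor the number of groups, so the table shows a range (equal-sized groups; simulation of 2 million values).

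| Assumed shape of factor | 2 groups | 3 groups | 4 groups |
|---|---|---|---|
| Uniform | 25% lost | 11% | 6% |
| Normal | 36% | 21% | 14% |
| Right-skewed (exponential) | 52% | 35% | 26% |

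Right skew is an assumption. It is plausible for pad weight, where entry requires only more than 1 g (section 2.3) and the pilot baseline means were 83.1 g and 85.5 g (section 2.7.1).

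**3. Power for the interaction.** Let δ be the change in treatment effect per SD of the factor. With 1:1 allocation, the noncentrality parameter is λ = δ² × N × 0.25 / SD², multiplied by the share of information kept. N = 96, SD = 48.87 g, two-sided 5%, noncentral F with 1 and 92 degrees of freedom.

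- δ = 28.4 g: λ = 806.56 × 24 / 2388.28 = 8.10, power 0.80 with the factor continuous. Median split: λ = 8.10 × 0.637 = 5.16, power 0.61.
- δ = 14.2 g: λ = 8.10 / 4 = 2.03, power 0.29 with the factor continuous. Median split: λ = 1.29, power 0.20.

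For three equal groups at δ = 28.4 g, power is 0.71 if the groups are scored as a trend and 0.60 if they are tested as unordered categories on 2 degrees of freedom.

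**4. Detectable interaction at 80% power (normal approximation).** Continuous: 48.87 × (1.960 + 0.842) / √24 = 27.9 g per SD. Median split: 27.9 / √0.637 = 35.0 g per SD.

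**5. The reverse case.** Suppose that the effect is constant on each side of the median and differs by 56.8 g between the halves. Then λ for the split is 56.8² × 0.25 × 24 / 2388.28 = 8.10 and power is 0.80, while a linear term in a normal factor keeps 2/π of this and has power of about 0.61. The ranking reverses.

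**The case against.** The strongest reply is that the article does not say how the subgroups will be formed or tested. Those details commonly belong in the statistical analysis plan, which is not shown, and nothing in section 2.7.2 rules out an interaction term. That is fair as far as cut points and tests go, and their absence is not the point here. What remains is that subgroup analysis is the method named and severity is expressly stratified.

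A reader might infer three stronger things, none of which the document supports:

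- **That grouping discards at least a third of the information.** This holds for a median split of a normal factor and for many splits of a skewed one. It does not hold for three or more equal groups of a normal factor, or for a median split of a uniform one.
- **That a continuous interaction is better at no cost.** It assumes a shape for the interaction, a few heavy leakers may have high leverage, a flexible form spends degrees of freedom, and a true step at the cut favours grouping.
- **That the plan will produce contradictory subgroup results half the time.** With a uniform effect of 28.4 g and 24 men per arm in each half, power within a half is 0.504, so the chance that exactly one half is significant is 2 × 0.504 × 0.496 = 0.50. This needs a median split and separate tests within each half, and the article states neither.

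It is also fair to say that 28.4 g per SD is a large interaction. Around an average benefit of 28.4 g, it means no benefit at one SD below the mean of the factor and 56.8 g at one SD above. For smaller interactions the absolute gain in power is modest.

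Finally, a man cannot reduce his leakage by more grams than he leaks at baseline. A gram-scale interaction with baseline pad weight can therefore reflect the scale alone. That is a reason for careful reading, not for grouping.

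**Conclusion.** The point stands as a modest improvement to an exploratory analysis. If the effect changes smoothly with the factor, grouping loses information: for a normal factor about 36%, 21% and 14% with two, three and four equal groups, and more under right skew. Under the illustrative 28.4 g per SD, a median split lowers interaction power from about 0.80 to 0.61. For moderate heterogeneity both approaches are weak.

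The figures rest on a linear interaction, the design SD used as the residual SD, 96 evaluable men and an assumed number of groups. Grouping is stated for pad weight and inferred for age and interval. The primary analysis and the sample size are not affected.

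**What to change.** Replace the subgroup sentence in section 2.7.2 with wording such as:

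> Heterogeneity will be assessed by adding a treatment-by-factor interaction to the primary model, one factor at a time, with age, time from surgery to enrollment and baseline 1-h pad weight kept as continuous variables. A simple non-linear form or a transformation will be allowed, and the influence of men with very high baseline leakage will be checked. The interaction estimate with its 95% CI and the week-6 treatment difference across the range of each factor will be reported. Categories will serve for display only, with no significance tests within them. The interaction with baseline pad weight will be interpreted with regard to the fact that the possible reduction in grams rises with baseline leakage.

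The cost is a change of wording: no new data, visits or patients. The downside is the assumed shape of the interaction, which the non-linear form and the displayed categories help to check, and some loss of efficiency if the effect truly steps at a threshold.

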## Discussion

3

Even with the minimally invasive approaches and the emerging functional preservation/reconstruction techniques, SUI is still one of the most frequently reported post-prostatectomy complications jeopardizing patients' quality of life (3, 19–23). The current treatment modalities for postoperative SUI are usually chosen according to the patients' preference, symptom duration, and severity. The noninvasive physiotherapies (i.e., pelvic floor muscle exercise, biofeedback, electrostimulation, and magnetic therapy) are the first choice for patients with short-term postoperative incontinence or those with mild-to-moderate leakage (24, 25). For non-responders to initial conservative management, surgical interventions are usually warranted, such as urethral bulking injection, sling procedure, proACT, and artificial urinary sphincter (25, 26). Take the so-called “gold standard treatment” artificial urinary sphincter for example, although it has achieved a high cure rate in the systematic review, it is also associated with several peri- and postoperative morbidities, including but not limited to infection, erosion, mechanical failure, and urethral atrophy (27, 28). Therefore, an effective treatment with less invasion and high safety features is expected to be validated for male SUI.

In previous multicenter, randomized clinical trials, EA has been substantiated to be an effective approach for SUI in women. It is superior compared with the sham EA treatment in reducing pad weight and incontinence episodes, with very few adverse events (7). It also offers additional benefits to the conventional PFME in improving SUI symptoms and quality of life in female with SUI (9). However, due to the different anatomical features and mechanisms of SUI between women and men, it is still innovative and imperative to investigate whether the same treatment modality is applicable to male SUI patients. It is known that the incidence of female SUI mostly results from urethral hypermobility and insufficient supportive force of the pelvic floor muscles due to advancing age or long-term sequelae of vaginal delivery. Intrinsic sphincter deficiency, which may lead to a more disastrous urinary leakage symptom, is the major cause of SUI in about 13% of female patients, according to the urodynamic report from the VALUE study (29). In clear contrast, SUI in men is usually secondary to iatrogenic or traumatic events, and could have more integrated etiological factors. For example, for those who undergo radical prostatectomy, at least five contributors have been proposed, namely, reduction of functional urethral length, loss of anterior suspensory and posterior supportive structures, denervation injury, and direct external urethral sphincter damage (3). Therefore, it is challenging but necessary to justify the application of EA for male SUI patients after radical prostatectomy. Although some sporadic reports (mostly from Chinese domestic journals) have revealed that the EA might be beneficial for male SUI, the overall quality of evidence was considered low and inconclusive (30). Therefore, we proposed the protocol for a randomized, placebo-controlled trial, aiming to provide a high level of evidence to justify the use of EA in male SUI.

Unique from the previous study design focused on the comparisons between EA and sham EA treatment, we exclusively investigate the add-on effects of EA in addition to the conventional PFME in accelerating continence restoration after radical prostatectomy compared with the PFME alone (31). Besides, since studies have revealed a pattern of time-dependent continence restoration with a duration as long as 12–24 months after procedure, it is of great importance to study whether the combination of EA and PFME could facilitate the early regain of continence to improve quality of life and to avoid later application of invasive procedures (32, 33).

Previous studies have confirmed the efficacy of EA using sacral and abdominal acupoints for SUI. According to Traditional Chinese Medicine theory, post-RP SUI results from kidney qi deficiency and sinking of middle qi. Zhongliao and Huiyang from the Bladder Meridian can strengthen the kidney qi, while Guanyuan, Zhongji, and Dahe are selected to elevate the middle qi and consolidate the lower jiao (34–36). BL33 and BL35 overlie the S2-S4 sacral nerves, which govern bladder function. RN3, RN4, and KI12 align with the T12-L1 spinal segments, influencing the hypogastric plexus. EA acts through multiple synergistic mechanisms, including normalizing bladder reflexes, strengthening pelvic muscles, enhancing connective tissue support, and reducing local inflammation, to restore urethral function and continence (37, 38).

Several advantages can be summarized based on the current design. To start with, the choice of standard 1-h pad test results as the primary outcome instead of the simple questionnaires aims to provide an objective and rigorous evaluation of the true value of EA. Besides, the follow-up timepoints are selected to validate both the temporal effects of EA during 3 and 6 weeks, and sustained effects at 10 and 18 weeks after treatment completion. It is also worth mentioning that our design not only validates the effectiveness of EA but also investigates its influence on the modification of pelvic floor structures using MRI to reveal the potential mechanisms of treatment. Moreover, the stringent protocol for sham EA will be applied, in which a pragmatic placebo needle with a blunt tip will be used to create a sense of stabbing, but without penetrating the skin. The use of a sticky pad to maintain the angle of needles maximally ensures the blinded settings for both groups.

To date, the benefits of EA as an adjunct to PFME for male patients with SUI remain insufficiently studied. This research gap could lead to inconclusive and ambiguous clinical decision-making on this potentially effective intervention. The completion of a high-quality trial with the proposed study design will provide high-level evidence to justify the future application of EA by presenting an alternative approach for SUI after radical prostatectomy.
